### Requiring level 2 or level 3 critical care

This is defined as requiring level 2 or 3 critical care (or obstetric HDU type care) as a result of an infection up until 6 weeks postnatally (days 0–42).

The endometritis outcomes are collected up until day 30 to be consistent with the CDC definition of endometritis, and the sepsis related outcomes are collected up until 6 weeks to be consistent with the national collection of post-natal sepsis.

### Patient-reported outcomes

These will be determined by the qualitative component of this feasibility study and reported as an outcome of the feasibility study along with summary statistics pre-specified in the statistical analysis plan.

## Participant withdrawal

Informed consent is defined as the process of learning the key facts about a clinical trial before deciding whether or not to participate. It is a continuous and dynamic process, and women should be asked about their ongoing willingness to continue participation with the telephone interviews before the interview questions commence. Women should be aware at the beginning that they can freely withdraw (discontinue participation) from the trial (or part of the trial) at any time.

Types of withdrawal as defined are as follows:

### Before the intervention

The woman would like to withdraw from trial treatment, before the intervention, is applied but is willing to be followed up in accordance with the schedule of assessments and if applicable using any central UK NHS bodies for long-term outcomes (i.e. the woman has agreed that data can be collected and used in the trial analysis).

### After the intervention

The woman would like to withdraw from the trial after the allocation is applied and does not wish to participate in the telephone interview but is willing to be followed up at any visits and if applicable using any central UK NHS bodies for long-term outcomes (i.e. the woman has agreed that data can be collected at standard visits and used in the trial analysis, including data collected as part of long-term outcomes).

### Without follow-up

The woman would like to withdraw from the trial after the allocation is applied and is not willing to be followed up in any way for the purposes of the trial and for no further data to be collected (i.e. only data collected prior to the withdrawal can be used in the trial analysis).

### Complete withdrawal

The woman wishes to withdraw completely (i.e. from trial treatment and all follow-ups) and is not willing to have any of their data, including that already collected, to be used in any future trial analysis.

## Adverse events and serious adverse events

The collection and reporting of adverse events (AEs) will be in accordance with the Research Governance Framework for Health and Social Care and the requirements of the Health Research Authority (HRA). No neonatal AEs or SAEs are required to be reported as the intervention is licenced for use in obstetrics over 34 weeks for swabbing as per the SmPC and has a demonstrated safety record in many trials in neonates above 34 weeks gestation [11].

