**Methods:**

This is a parallel group feasibility randomised controlled trial comparing vaginal cleansing using chlorhexidine gluconate versus no cleansing (standard practice) at CS to reduce infection. Women will be recruited from four National Health Service maternity units. Two hundred fifty women (125 in each arm) undergoing elective or emergency CS, who are aged 16 years and above, and at least 34 weeks pregnant will be randomised. Allocation to treatment will be on a 1:1 ratio. The study includes a qualitative aspect to develop women centred outcomes of wellbeing after delivery.

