### Justification for intervention

Prophylactic antibiotics at the time of surgery have been demonstrated to be beneficial in a number of large randomised controlled trials (RCT) and continue to reduce infection rates [1]. Current practice of skin preparation [2] is guided by a recent RCT demonstrating the superiority of a chlorhexidine over an iodine-based solution [3]. In addition to skin preparation with an antiseptic solution, cleansing inside the vagina with povidone iodine has been evaluated [4]. A Cochrane review of seven trials randomising 2816 women (2635 analysed) estimated the effects of vaginal cleansing (all with povidone-iodine) on post-caesarean infectious morbidity [4]. Vaginal preparation immediately before caesarean delivery significantly reduced the incidence of post-caesarean endometritis from 8.3% in control groups to 4.3% in vaginal cleansing groups (average risk ratio (RR) 0.45, 95% confidence interval (CI) 0.25 to 0.81, seven trials, 2635 women). The risk reduction was particularly strong for women who were already in labour at the time of the caesarean delivery (7.4% in the vaginal cleansing group versus 13.0% in the control group; RR 0.56, 95% CI 0.34 to 0.95, three trials, 523 women) and for women with ruptured membranes (4.3% in the vaginal cleansing group versus 17.9% in the control group; RR 0.24, 95% CI 0.10 to 0.55, three trials, 272 women [4]). The above would appear an effective and important strategy to reduce morbidity at CS, yet this has not been adopted within obstetric practice internationally and does not feature within the NICE Intrapartum guideline [5]. This is due to concerns with exposure of the fetus to iodine-based substances, concerns with vaginal staining and allergy to iodine. Iodine is a recognised antibacterial agent, but inactivity by the presence of blood [6] limits its use. Thus, there are a number of reasons to believe that vaginal cleansing with chlorhexidine would be an appropriate alternative to povidone iodine. Some studies show greater reduction in skin flora after application of chlorhexidine (0.5 and 4%) [6] compared with povidone-iodine agents. Also, chlorhexidine may have a greater residual activity after application than other preparations and, unlike povidone iodine, it is not inactivated by the presence of blood. Solutions that contain lower concentrations, such as the commonly used chlorhexidine gluconate and acetate (0.05%), are usually well tolerated and may be used for vaginal preparation [6]. With this preparation, there are no reported cases of allergy. There is one small randomised controlled trial comparing povidone iodine with chlorohexidine gluconate for vaginal cleansing at CS. This suggested that chlorohexidine may be superior, and further research was needed [7].

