### Identification of participants

Given recruitment, consent and randomisation processes will differ for emergency and elective CS due to differences in planning for surgery; the processes for each type of surgery will be detailed separately. All women booking at any of the hospitals over the study period and who are greater than 34 weeks pregnant while recruitment is running will be posted a patient information leaflet. This is to ensure that all women are aware of the study before delivery of their baby/babies. This will be accompanied with patient information leaflets and study information being available in antenatal clinics and triage waiting rooms. Study posters will also be displayed in prominent positions through the hospitals.

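### The neonatal safety waiver makes no exception for a serious event judged related to the vaginal antiseptic, and its stated grounds stop just short of the lowest eligible gestation

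*Protocol article*

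**What the plan says.** The opening paragraph of Adverse events and serious adverse events in the protocol article sets the rule and its first ground together: "No neonatal AEs or SAEs are required to be reported as the intervention is licenced for use in obstetrics over 34 weeks for swabbing". The second ground is a "demonstrated safety record in many trials in neonates above 34 weeks gestation". No category of neonatal event is held back from the exemption.

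The Serious adverse events (SAE) section sets out the form, the causality scale, the 24-hour report to the trials office and the 15-day report of unexpected related events to the ethics committee. The process starts when a woman has had such an event. A longer stay caused by neonatal complications is listed among the events that do not count as SAEs. The section ends with a general duty to tell the ethics committee and sponsor at once if a significant safety issue comes to light.

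On gestation, the abstract says that women "at least 34 weeks pregnant will be randomised", and the Eligibility criteria and co-enrolment section likewise includes 34 weeks. The Identification of participants section sends leaflets to women "who are greater than 34 weeks pregnant while recruitment is running", but that governs mailing and not eligibility.

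**The concern.** A licence and an existing safety record are reasonable grounds for not collecting routine neonatal events. They are weaker grounds for also exempting the rare event that is both serious and judged to be caused by the study antiseptic, which is the kind of event that SAE reporting exists to catch. The plan names an allergic reaction to chlorhexidine needing treatment as an SAE. Under the waiver, the same reaction in an exposed baby would create no duty to report.

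At stake is whether the trials office, the oversight committee and the ethics committee would hear of such an event before a definitive trial exposes more babies. A lesser matter is that the reasons given for the waiver do not, as worded, reach every baby it covers.

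**Working it through.** **Is there any other route for a neonatal event?**

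| Place in the protocol article | Covers the baby? |
|---|---|
| Adverse events and serious adverse events, opening paragraph | Expressly exempts neonatal AEs and SAEs |
| Serious adverse events (SAE), reporting steps | Written for the woman |
| Same section, list of events not counted | Removes prolonged stay due to neonatal complications |
| Clinical outcomes (endometritis by CDC definition, clinical endometritis, sepsis, length of stay, readmission, antibiotics, critical care) | All maternal |
| Serious adverse events (SAE), last sentence | Not limited to the mother, but applies only once a significant issue has been identified |

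One unsystematic route therefore remains.

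**Gestation wording.** The waiver's grounds are stated for gestation greater than 34 weeks; eligibility is 34 weeks or more. Read literally, they differ at one boundary point. The article gives no gestation distribution, so the number of babies affected cannot be computed and may be zero.

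**What could about 125 exposed babies show?** The plan gives no neonatal event rate or precision figure to reproduce. The input is 125 women per arm (abstract, Methods), assuming one baby per woman and that all allocated women are treated.

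- Upper limit after zero events, one-sided 95%: 1 − 0.05^(1/125) = 2.4%.
- Limit from a two-sided 95% interval: 1 − 0.025^(1/125) = 2.9%.
- With 112 babies instead of 125 (about 10% fewer), one-sided: 1 − 0.05^(1/112) = 2.6%.

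Chance of at least one event of any cause, 1 − (1 − r)^125, at assumed true rates r:

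| r (assumed) | Chance |
|---|---|
| 0.1% | 12% |
| 0.5% | 47% |
| 1% | 72% |
| 2% | 92% |

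These rates are not in the article, and they count any event, not events judged related. They do not say how many reports the proposed rule would produce.

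**Scale of the next step.** The Sample size section gives 1548 women, or 1720 after allowing for 10% loss. Both reproduce: the two-sided pooled formula for 8.3% versus 4.3% at 90% power gives 774 per arm, 2 × 774 = 1548, and 1548/0.9 = 1720. The cleansing arm would then hold 774 to 860 women (1548/2 to 1720/2). Whether the waiver would carry over to that trial is not stated.

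**The case against.** The waiver is explicit and reasoned, and neonatal safety is not among the study's objectives. That stands, and it is why routine neonatal events should remain exempt. Several stronger readings are tempting, but the document does not support them.

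- **Serious harm to a baby would go unreported because of the gestation mismatch.** The gap comes from the waiver and would be the same if the wording matched. The text says reporting is not required; it does not forbid it. The significant-safety-issue notice also remains.
- **The trial learns nothing about neonatal safety.** It plans no systematic neonatal data, which is a narrower statement. Full capture in about 125 babies would also tell little.
- **The case for chlorhexidine rests on neonatal safety.** The passage on why cleansing was not adopted reads "This is due to concerns with exposure of the fetus to iodine-based substances", so the concern is specific to iodine. The stated advantages of chlorhexidine concern antibacterial activity, tolerability and absence of reported allergy.
- **The safety basis is thin.** It is true that "There is one small randomised controlled trial comparing povidone iodine with chlorohexidine gluconate for vaginal cleansing at CS", but the waiver cites the product licence and neonatal trials instead. Those sources are not at hand and cannot be judged here. The review of cleansing at vaginal birth, which the article also cites, reported no safety concern for mother or baby.

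The full protocol is not shown. If it already contains an exception for related serious neonatal events, the article's unqualified sentence is what needs correcting.

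**Conclusion.** The concern holds in a limited form. As written, a serious neonatal event judged related to the antiseptic need not be reported through the SAE process. The one remaining route has no neonatal collection behind it. The gestation mismatch is real but confined to the boundary, and it may be loose wording.

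The gain from a change is a route by which a related serious event becomes known before the definitive trial. It is not a safety estimate: even complete capture with zero events would exclude only rates above about 2.4% (one-sided 95%), assuming 125 exposed single babies. Nor would reports limited to related events allow a comparison between arms. This is an inexpensive improvement to patient safety, not a flaw that undermines the feasibility objectives.

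**What to change.** Keep the exemption for routine neonatal events. Add that a neonatal event which meets the serious definition and is judged possibly, probably or definitely related to the vaginal antiseptic is reported on the existing SAE form, with the existing causality review and onward reporting. Extend the wording that starts the SAE process from the woman to the woman or her baby for this purpose.

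Reconcile the gestation wording of the safety section with the eligibility criteria, so that the stated grounds cover every baby enrolled. Which limit is right is for the sponsor to settle.

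The cost is a short amendment and probably a few extra SAE forms over about 250 births, with no added participants or visits. Recording neonatal death and unexpected neonatal-unit admission by arm would be optional. The Blinding section describes data collection from maternal notes, so the cost of obtaining those items has not been shown to be small.

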### Adverse events (AE)

There are certain AEs which are commonly expected in participants as a result of pregnancy and/or CS. As these events are well characterised, it is highly unlikely that this trial will reveal any new safety information relating to this intervention. Thus, there will be no AEs recorded.

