### Serious adverse events (SAE)

All events which meet the definition of serious will be collected and recorded in the participant notes and the Case Report Form (CRF). SAEs will, in addition, be reported to the trials office immediately and within 24 h of the principal investigator being made aware of the event. Allergic reaction to chlorohexidine requiring treatment will be considered a serious adverse advent.

Events not considered an SAE in PREPS include:Hospitalisation for delivery of the babyThe development of infection and sepsis in the post-natal period that requires inpatient treatment or prolongation of hospitalisation as this is an outcome of the trialObstetric haemorrhageDamage to bowel or bladder during surgeryProlonged hospitalisation due to neonatal complicationsThromboembolic events

All other events not detailed above that meet the definition of a SAE should be reported as detailed below.

SAEs should be reported on an SAE Form. When completing the form, the PI will be asked to define the causality and the severity of the SAE. Causality will be assessed as definitely related, probably related, possibly related, unlikely to be related or unrelated. On becoming aware that a woman has experienced an SAE, the Investigator *or delegate(s)* should report the SAE to their own Trust in accordance with local practice and to the BCTU trials office. On receipt of an SAE form, the Chief Investigator (CI) or delegate(s) will independently determine the seriousness and causality of the SAE. An SAE judged by the PI or CI or delegate(s) to have a reasonable causal relationship with the intervention will be regarded as a related SAE. The causality assessment given by the PI will not be downgraded by the CI or delegate(s). If the CI or delegate(s) disagrees with the PI’s causality assessment, the opinion of both parties will be documented, and where the event requires further reporting, the opinion will be provided with the report. The CI *“or delegate(s)”* will also assess all related SAEs for expectedness. If the event is unexpected (i.e. is not defined in the protocol as an expected event), it will be classified as an unexpected and related SAE. BCTU will report all events categorised as unexpected and related SAEs to the main Research Ethics Committee (REC) within 15 days. The main REC and sponsor will be notified immediately if a significant safety issue is identified during the course of the trial.

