## Sample size and data analysis

### Sample size

Since this is a feasibility study, no formal sample size calculations have been undertaken. The feasibility study is not designed or powered to detect a statistically significant difference in efficacy between the two treatment arms. A total sample size of 250 participants would agree with existing literature which suggests that the size of the feasibility study should be at least 10% of the anticipated size of the substantive study [12]. A recruitment target of 250 participants has been chosen for this feasibility study as we expect this number will be sufficient to provide estimates of the feasibility outcomes.

Preliminary sample size calculations were computed for the full RCT. Vaginal cleansing with povidone iodine has been evaluated in a Cochrane review which comprised of seven trials randomising 2816 women (2635 analysed) estimating the effects of vaginal cleansing (povidone-iodine) on post-caesarean infectious morbidity. The risk of bias was generally low, with the quality of most of the studies being high. Vaginal preparation immediately before caesarean delivery significantly reduced the incidence of post-caesarean endometritis from 8.3% in control groups to 4.3% in vaginal cleansing groups. To detect a difference of this size with 90% power and alpha at 5%, we would require 1548 participants. In addition, to account for an anticipated 10% loss to follow-up, we would need a total of 1720 participants.

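### The no-AE rule also drops untreated reactions to chlorhexidine, and the SAE exemptions for haemorrhage and thromboembolism set no limit for fatal or related cases

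*Protocol article*

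**What the plan says.** The section Adverse events (AE) starts from background events: "There are certain AEs which are commonly expected in participants as a result of pregnancy and/or CS". It argues that, because these are well characterised, the trial is unlikely to reveal anything new about the safety of the intervention. It concludes: "Thus, there will be no AEs recorded".

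The section Serious adverse events (SAE) opens with a wide rule: "All events which meet the definition of serious will be collected and recorded in the participant notes and the Case Report Form (CRF"). SAEs are, in addition, to be reported to the trials office within 24 hours. One reaction to the intervention is given SAE status by name: "Allergic reaction to chlorohexidine requiring treatment will be considered a serious adverse advent" (read here as event).

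A list of events not considered SAEs follows. Obstetric haemorrhage and thromboembolic events appear on it by category alone. The infection and sepsis item is worded by its consequence: inpatient treatment or a longer stay. The list closes with: "All other events not detailed above that meet the definition of a SAE should be reported as detailed below". Causality and severity are assigned when the SAE form is completed. The chief investigator's review and the expectedness assessment follow from that form.

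**The concern.** There are two separate problems, and both lie in rules that the article states outright.

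First, the premise of the no-AE rule is narrower than its conclusion. Knowing the usual complications of pregnancy and caesarean section says nothing about how women react to vaginal chlorhexidine. The rule nevertheless removes every non-serious event, including those that only the intervention could cause. This matters because Justification for intervention gives staining and allergy among the reasons why iodine cleansing was not taken up, and presents low-strength chlorhexidine as well tolerated. The trial would discard the milder evidence on that point in its own population.

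Second, two exempt categories have no limit by outcome or by suspected relation to the intervention. On the literal text, a fatal embolism, or a haemorrhage that an investigator thought related, needs no SAE form. It would then miss the causality and expectedness review that depends on the form.

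**Working it through.** **1. What each rule captures.** This sets the two safety sections side by side.

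| Event | Rule that applies | Result |
|---|---|---|
| Allergic reaction to chlorhexidine, treated | Named as an SAE | Recorded and reported |
| Allergic reaction, untreated and not otherwise serious | No-AE rule | Not recorded |
| Local irritation, not serious | No-AE rule | Not recorded |
| Other serious reaction, not on the exempt list | Residual SAE rule | Recorded and reported |
| Infection or sepsis needing inpatient care | Exempt, limited by consequence | Collected as an outcome |
| Haemorrhage or thromboembolism, fatal or thought related | Exempt by category, but the opening sentence says all serious events are recorded | Recording required by one sentence; no SAE form |

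The second and third rows are the gap left by the no-AE rule. The last row is the conflict within the SAE section. Maternal death is not among the listed clinical outcomes, so the opening sentence is the only text in the article that requires such a death to be recorded.

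**2. Size of the first gap.** The arm size comes from the abstract: "Two hundred fifty women (125 in each arm"). The protocol gives no reaction rate, so the rates below are assumptions.

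- Expected cases = 125 × p. At 1%: 1.25. At 5%: 6.25. At 10%: 12.5.
- Chance of at least one case = 1 − (1 − p)^125. At 1%: 72%. At 2%: 92%. At 5%: over 99%.
- If no case were seen, the one-sided 95% upper bound = 1 − 0.05^(1/125) = 2.4%.

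One arm of this trial could therefore give a rough but usable estimate of common mild reactions. These counts cover all reactions. Any that were treated allergies would already be captured, so the number lost is at most these figures.

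**3. Carry-over to the definitive trial.** The section Sample size plans to detect a fall "from 8.3% in control groups to 4.3% in vaginal cleansing groups", and states that "with 90% power and alpha at 5%, we would require 1548 participants". With a two-sided 5% test, pooled variance under the null and no continuity correction, and with mean rate 0.063:

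- n per arm = [1.960 × √(2 × 0.063 × 0.937) + 1.282 × √(0.083 × 0.917 + 0.043 × 0.957)]² / 0.040² = 773.3, rounded up to 774.
- Total = 2 × 774 = 1548. With 10% loss, 1548 / 0.90 = 1720.

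Both stated figures reproduce. They matter here only for scale: under Traffic light system, a green result means proceeding with the protocol unchanged (unless the focus groups clearly point to an improvement), so the same safety rules would pass to a trial of about 1720 women.

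**The case against.** The case for leaving the rules alone is substantial.

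- **Support for light safety collection.** Justification for intervention says that low-strength solutions are usually well tolerated with no reported allergy, and that trials of vaginal cleansing in normal delivery raised no safety concern. The section Intervention cites a formulary indication for obstetric swabbing. Collecting serious events plus treated allergy is a proportionate choice for an established antiseptic. This stands as a defence of the choice, though it is not the reason that the AE section gives.
- **Not an objective.** Tolerability is not among the aims or the stop-go criteria. This stands, and it limits how much weight the point can bear.
- **Condensed article.** The definition of serious is not reproduced, so the full protocol may hold a rule on deaths. This also stands. What can be criticised is the wording printed here.
- **Risk to blinding.** Asking about vaginal reactions could prompt the guess about allocation that closes the 14-day interview. This is correct, and it decides where a new item must go.

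A reader might infer that some maternal deaths would go unrecorded and would never reach the oversight committee. The documents do not support this. The opening SAE sentence requires serious events to be recorded in the notes and CRF, and reporting is described as a further step. Nothing limits the committee to SAE forms, and a significant safety issue must be notified at once to the ethics committee and the sponsor. A reader might also infer that tolerability cannot be estimated at all. That goes too far as well, since treated allergic reactions and other serious reactions are captured.

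**Conclusion.** The point holds in a limited form. The stated reason does not cover reactions specific to the intervention, and untreated allergic reactions and non-serious local irritation are not recorded as a result. The exemptions for haemorrhage and thromboembolism set no limit for fatal or related cases, so such cases could escape SAE reporting and causality review. The exemption list and the opening sentence of the SAE section must be reconciled.

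The size is modest. The first gap is at most about 1 to 13 unrecorded reactions in the cleansing arm, and that rests wholly on an assumed rate of 1% to 10%. The second is very unlikely to matter among 250 women and gains weight only if the wording passes to the definitive trial. No stated objective or stop-go criterion is affected. It is worth correcting because the change is cheap.

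**What to change.** 1. Restrict the no-AE rule to events expected from pregnancy or caesarean section.
2. Record local vaginal or skin reactions and any allergic reaction as targeted events, using one item in the 14-day telephone interview. Word it identically in both arms, and place it after the question on which treatment the woman thinks she received.
3. Qualify the exemption list so that an event that is fatal, or judged related to the intervention, is still reported as an SAE. State that exempt serious events remain recorded in the notes and CRF, so that the list agrees with the section's opening sentence.

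The cost is one interview item, one qualifying phrase, slightly more data entry and, rarely, an extra SAE report. Placing the item after the guess question protects the blinding assessment. The trial was already recruiting when the article was submitted, so if it is too late to amend, the changes belong in the protocol of the definitive trial.
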